### **Intervention**

#### **ACT group therapy**

Ten 90-minute sessions will be delivered weekly by a clinical psychologist trained in bariatric psychological support and ACT. Components of the intervention are shown in Table 1. The ACT intervention has been adapted from a manual used in a previous pilot trial for bariatric surgery patients who experienced weight regain. The following adaptations were made by ACT trained members of the research team (EB, DLB) and agreed with the multidisciplinary team and service user advisors: (1) Reduced emphasis on eating behaviours and increased emphasis on living in line with personal values. For instance, the necessity for daily weigh-ins, calorie counting, and food recording for all participants has been removed. Instead, participants are encouraged to set personalised, achievable goals (which may or may not involve specific eating behaviours) which move them towards their self-defined values. The manual includes support to enhance values clarity. (2) A stance of self-compassion is actively encouraged throughout the intervention.

The intervention focuses on fostering key ACT processes, including acceptance of difficult internal processes (e.g., thoughts, feelings, urges), defusion from thoughts, values clarification, willingness and committed action, self as context and linking values to present moment decision-making. The aim is to enhance participants’ ability to adhere to the restrictive postoperative diet in order to prevent weight regain whilst maintaining or improving quality of life.

As part of the intervention, each week participants complete two measures of ACT processes: The Bullseye (adapted from Lundgren’s Bullseye Worksheet (2012)) which facilitates values clarification and prompts them to consider how closely they are living in line with their values, and the CompACT: a brief measure of ACT processes designed for clinical and research use. The intervention also includes standard psychoeducation and behavioural interventions for weight management post-bariatric surgery. Homework is set and reviewed weekly to reinforce in-session learning. In addition, and at the therapist’s discretion, participants are alerted to reinforcing resources such as ACT-relevant ‘YouTube’ videos.

**Table 1: ACT intervention components.**

| Session | Psychoeducation and behavioural components | Acceptance-based components                          |
|---------|--------------------------------------------|------------------------------------------------------|
| 1       | Programme overview                         | Limitations of experiential avoidance                |
| 2       | Energy balance                             | Acceptance as the alternative to control             |
|         | Postoperative nutrition information        | Introducing willingness                              |
| 3       | Physical activity guidelines               | Review of acceptance and willingness                 |
|         |                                            | Willingness skills continued                         |
|         |                                            | Values clarification                                 |
| 4       | Challenges of obesogenic environment       | Incorporating values into behaviour                  |
|         | Portion control                            | Behavioural flexibility                              |
| 5       | Protein intake after surgery               | The problem with mindless eating                     |
|         |                                            | Mindful decision-making                              |
| 6       | Handling holidays, weekends and vacations  | Defusion (i.e., cognitive distancing)                |
| 7       | Slowing down rate of eating                | Strategies to help defusion and increase willingness |
|         | Decreasing grazing                         |                                                      |
| 8       | Decreasing fat intake                      | Defusion review                                      |
|         |                                            | Urge surfing                                         |
| 9       | Preparing for the end of group             | Review of major concepts                             |
|         | Distinction between lapse and relapse      | Responding to decreased motivation in the long term  |
| 10      | Congratulations                            | Continued commitment                                 |
|         |                                            | Final review of concepts                             |

**Control**

*Usual care support group*

The usual care support group will comprise 10 consecutive weeks of 90-minute support groups (current usual care), coordinated by a psychology graduate with no formal therapy training. The groups will be unstructured to allow patients to talk about their difficulties in a minimally facilitated way. If patients request specific advice, self-help guidance, signposting to appropriate sources of help and onward referral to specialist services will be provided. The usual care support group will be held at the same time and venue as the ACT group, but on a different day of the week.

**Treatment fidelity**

The psychologist delivering the ACT intervention will receive supervision from the members of the study team who have experience delivering ACT (EB) and working with bariatric patients (SS). A sample of sessions will be observed by a member of the study team trained in ACT (EB) and assessed for fidelity to the manual using a published rating scale adapted for this trial. Deviations from the manual will be recorded and addressed in supervision.

**Data collection and measures**

A standardised battery of measures will be completed at baseline, three, six and 12 month follow up, except for weight and the King’s Obesity Staging Criteria which will be collected at baseline and 12 month follow up only to allow for meaningful change. Demographic data: self-reported medical history, age, gender, work status, educational level, ethnicity, marital status, number of dependents, current or past psychological therapy and current medications, will also be collected at baseline. Baseline and 12 month follow up data will be collected face to face to coincide with routine clinic appointments; three and six month follow up data will be collected via telephone.

*Primary outcome measures*

The primary outcome is the feasibility of the trial methodology. This will be measured by, (1) The willingness of participants to be randomised, measured by recording the number of participants who drop out of the study after they have been randomised, (2) the number of eligible patients attending clinic, as assessed by calculating the percentage of patients who meet eligibility criteria at screening, (3) follow-up rates, assessed by the percentage of participants retained until 12 month follow-up and providing complete datasets, (4) adherence to the intervention or control, assessed by number of sessions attended, (5) reasons for attrition, (6) the time needed to collect data and (7) the acceptability of the intervention at 12 month follow-up, as assessed by a 5 point likert scale (1=“Not at all”, 3=“somewhat”, 5=“Very”) to evaluate how helpful participants found the treatment, their satisfaction with it, and how likely they would be to recommend it to a friend and (8) the standard deviation of weight maintenance (<5% weight gain from baseline assessment) or weight loss, in order to estimate the required sample size for a future trial (measured at study close-out).

*Secondary outcome measures*

Outcomes relating to (A) obesity, health and wellbeing, (B) costs, and (C) measures of ACT processes will be collected to test the appropriateness and acceptability of measurement instruments to be used as outcomes in a full trial. The validated instruments to be used are listed below.

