**ABSTRACT Background:** Bariatric surgery is an effective treatment for obesity. However, around one in five people experience significant weight regain. In the months following surgery, loss of food as a hedonic reward, increased sensitivity to food-related cues, alcohol use and depression may translate into new obesogenic behaviours which can be targeted in therapy. Acceptance and Commitment Therapy (ACT) teaches acceptance of and defusion from thoughts and feelings which influence behaviour, and commitment to act in line with personal values. We will test whether people who have had bariatric surgery over one year ago find 10 weeks of ACT group therapy an acceptable treatment and whether a larger trial to test whether ACT can improve long-term post-operative outcomes would be feasible. **Methods:** This will be a feasibility randomised controlled trial (RCT) with participants randomised to either ACT or a Usual Care Support Group control. Participants will be recruited at 15-18 months post-surgery and compared at baseline, 3, 6 and 12 months. The trial will provide information about recruitment and characteristics of the proposed outcome measures to inform a definitive RCT. **Conclusions:** Trials big enough to determine whether a treatment approach works are costly, so this small study will help determine whether the methods used, such as how people are recruited, allocated to groups, and how data are collected, are likely to work on a bigger scale. This project is the first step in testing whether ACT can help people who have had bariatric surgery. **Trial Registration:** Researchregistry.com, UIN: 3959 (date registered: 10 April 2018); ISRCTN registry ID: ISRCTN52074801.

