#### ***Exclusion criteria***

Suicidal ideation (score of  $>0$  on Question 9, PHQ-9). Patients who are unable to communicate in English as the intervention is delivered in English and unable to commit to attendance to 10 sessions.

Potentially eligible participants will be provided with a Participant Information Sheet (PIS) and a PHQ-9 to screen for suicidal ideation by a clinician at their regular follow-up appointment. Patients who do not attend will be posted the PIS with their routine appointment reminder letter to avoid selection-bias.

Eligible patients attending the clinic for their routine follow up appointment, who verbally express an interest in participating in the study will be approached by a researcher after their appointment and invited to read through the PIS. They will have the opportunity to ask questions about the study and, if the patient wishes to participate, an appointment will be made with the researcher to obtain written consent, and for baseline data collection and randomisation.

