#### *Statistical data analysis*

Analyses will be undertaken using R program. All significance tests will be 2-tailed and alpha will be set at  $p < 0.05$ . The distribution of the study population will be characterised using descriptive summary statistic parameters, that is median, range, mean, and standard deviation. Then, we propose to use ANCOVA to calculate variations within primary and secondary outcome measures pre-treatment and at follow-up. Anonymised data from those who decline to participate will also be reported. Complete case analysis and intent-to-treat analyses (using last measurement carried forward for participants who provided baseline assessment measurements) will be conducted.

A cost-consequence analysis (CCA) will be carried out from a National Health Service (NHS) perspective. This involves listing the costs and outcomes associated with ACT and the Usual Care Support Group separately, allowing decision-makers to compare the relative value of approaches, and by calculating resource use. The intervention costs will be calculated based on the activities involved in delivering the programme such as staff salaries, administrative and managerial costs.

Total costs of the individuals in the two groups will be compared and estimated by multiplying the resource use with the unit costs of health and social care. We will present the additional costs associated with the intervention and present the costs alongside the benefits (if any) identified in the trial. Sensitivity analyses to model uncertainties around all key cost and outcome parameters, and plausible ranges will be specified using information from the trial and from the literature specific to the population in the study will be conducted.

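### Primary outcome item (1) measures willingness to be randomised by drop-out after randomisation, so it counts attrition, and no primary item is an acceptance rate.

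*Protocol*

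**What the plan says.** Protocol, Data collection and measures, Primary outcome measures, makes feasibility of the trial methods the primary outcome and lists eight components. Four matter here:

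- Item (1): "willingness of participants to be randomised, measured by recording the number of participants who drop out of the study after they have been randomised".
- Item (2), on eligible clinic attenders, assessed by "calculating the percentage of patients who meet eligibility criteria at screening".
- Item (3): "follow-up rates, assessed by the percentage of participants retained until 12 month follow-up and providing complete datasets".
- Item (5): "reasons for attrition".

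The recruitment pathway is under Exclusion criteria. A clinician gives potentially eligible patients the Participant Information Sheet (PIS) at routine follow-up, and patients who do not attend are sent it by post. The researcher sees only those eligible attenders who have already said they are interested. For a patient who then wants to take part, "an appointment will be made with the researcher to obtain written consent, and for baseline data collection and randomisation". Under Randomisation, the study clinician tells the participant the allocation afterwards.

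Two other statements bear on the point. The Abstract says "The trial will provide information about recruitment and characteristics of the proposed outcome measures". Statistical data analysis says "Anonymised data from those who decline to participate will also be reported".

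**The concern.** The quantity named in item (1) is settled before randomisation; the quantity counted arises after it. A patient who does not want treatment chosen by chance declines at the clinic visit or the consent appointment and never enters the count. A patient who accepts randomisation and moves away at month nine does enter it. The item therefore records loss after randomisation under the label of willingness.

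The share of eligible patients who accept randomisation drives the recruitment time and number of sites for the definitive trial, which is what a feasibility study should establish. If it is not defined as a measure, the numbers and reasons needed for it may not be logged when the study is offered, and reasons for refusal are hard to recover later.

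**Working it through.** **Step 1. Who can be counted.** The order in the protocol is: PIS from the clinician; interest expressed; researcher contact; consent, baseline and randomisation; allocation disclosed; follow-up to 12 months. Refusal of randomisation falls before the randomisation step. Item (1) counts only events after it. It sets no time limit and no restriction on reason, so leaving on hearing the allocation and any later withdrawal count alike.

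**Step 2. Whether another primary item fills the gap.** Item (2) is the share eligible, not the share accepting. Item (3) is retention, so item (1) is largely its complement. Item (5) gives the reasons for the same losses. Items (4), (6), (7) and (8) concern sessions attended, data-collection time, acceptability of the intervention, and the variability of the weight outcome. None is an acceptance rate.

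**Step 3. How far acceptance can vary while item (1) stays fixed.** There is no stated acceptance figure to reproduce. The inputs from Sample size are 58 to be recruited and 30% estimated loss. The number of eligible patients offered the study, N, is not given, so the values below are assumptions.

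Item (1) as written: 0.30 × 58 = 17.4, about 17 participants.

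Acceptance: p = 58/N, with the Wilson 95% interval

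[p + z²/(2N) ± z·√(p(1−p)/N + z²/(4N²))] / (1 + z²/N), z = 1.96.

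For N = 70: p = 0.829 and the interval is (0.856 ± 0.092)/1.055 = 0.724 to 0.899.

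For N = 300: p = 0.193 and the interval is (0.200 ± 0.045)/1.013 = 0.153 to 0.242.

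| Eligible and offered the study (assumed) | Randomised | Acceptance (95% CI) | Item (1) at 30% loss |
|---|---|---|---|
| 70 | 58 | 83% (72-90%) | about 17 |
| 116 | 58 | 50% (41-59%) | about 17 |
| 300 | 58 | 19% (15-24%) | about 17 |

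Item (1) does not separate a trial that most eligible patients join from one that most refuse.

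**Step 4. Which denominator would work.** Dividing by the patients whom the researcher approaches would leave out anyone who declined to the clinician, because the researcher meets only those already interested. Dividing by eligible patients without qualification has a similar problem: Inclusion criteria make willingness to consent a condition of eligibility, so a refuser could be classed as ineligible. The denominator has to be set at the point where the PIS is handed over, with the willingness criterion set aside.

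**The case against.** Three objections have force.

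First, item (1) is not empty. Participants are not blinded and are told their arm, so leaving at that moment is some evidence of unwillingness to accept a random allocation. That stands, and a reader who concluded that the item carries no relevant information would go too far. But the item does not isolate those withdrawals from other losses.

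Second, a reader might infer that the trial could report good willingness while heavy refusal stayed hidden. The protocol does not support this. Data on decliners are to be reported, item (2) requires counts of patients screened and eligible, and the number randomised will be known. A rough rate could probably be put together and heavy refusal would be at least partly visible. What remains is that the rate is not defined, has no denominator and is not tied to item (1).

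Third, a reader might extend the criticism to item (3), which joins retention to complete data, and infer that it would misstate the attrition carried into the next sample size. That does not follow: Sample size provides separately for recording loss to follow-up and attrition, with reasons, for the definitive trial's power calculation. The size of any gap also depends on assumptions. With 70% retained and each of the 15 listed measures assumed 97% complete, the joint figure is 0.70 × 0.97^15 = 44% if gaps are independent, but 0.70 × 0.97 = 68% if the same patients miss everything. The wording can also be read as two separate quantities.

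A later analysis plan does not answer the main point, because the protocol itself already fixes the measure for item (1).

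**Conclusion.** The point holds for item (1). The protocol names willingness to be randomised and fixes a measure of attrition in its place, largely duplicating items (3) and (5), and it defines no acceptance rate among its primary outcomes. In the illustration, acceptance runs from 83% down to 19% while item (1) stays at about 17. The denominators of 70 and 300 are assumed; only the 58 and the 30% come from the protocol. The conclusion itself rests on the order of events in the recruitment pathway, not on those denominators. No sample size, power figure or treatment comparison changes. Item (3) is not part of the finding, beyond the advice that retention and completeness are clearer as two figures.

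**What to change.** Redefine item (1) as the number randomised divided by all screened patients who meet the eligibility criteria other than willingness to consent and who were given the PIS in clinic. Report it with a 95% confidence interval and with reasons for declining, including not wanting to be randomised. Report patients who were posted the PIS separately, since their eligibility and response are learned by a different route.

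Report drop-out after randomisation only under items (3) and (5), and there identify withdrawals made on learning the allocation. Optionally, give retention and dataset completeness under item (3) as two figures.

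The cost is a rewritten sentence in the protocol, a reason-for-declining field on the screening log, and a note there of whether the PIS was handed over or posted. Data on decliners are already due to be reported, so no new data stream is needed. The log field should be in place while patients are being invited.

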### **Sample size**

As this is a feasibility study and no hypothesis testing will occur, a power calculation has not been conducted. Sample sizes between 24 and 50 have been recommended for feasibility studies, however to allow for loss to follow up, estimated at 30%, we will aim to recruit 58 participants. Loss to follow up and intervention and Usual Care Support Group attrition, including reasons, will be recorded to inform power calculations for a definitive RCT. This information will be recorded in a consort diagram.

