#### *Tertiary qualitative outcomes*

A nested qualitative, semi-structured interview study will be conducted with 12 participants (six ACT; six control) following the 12 month follow-up in order to understand the 'what, why and how come' of participants' beliefs and behaviours in order to inform the design and delivery of a future full RCT. A topic guide will prompt participants to discuss their experience of participation in the study and in the groups. The topic guide will be informed by the study and intervention processes, observations made by the study team, study psychologist, Usual Care Support Group co-ordinator and participants during the groups. It will be developed with service user advisors and will take approximately 1 hour to complete. Interviews will be recorded and transcribed verbatim.

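### Acceptability, a primary measure and the first stated aim, is rated only once, at 12 months, so participants lost before then never rate a 10-week treatment

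*Protocol*

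**What the plan says.** The Abstract gives as the first question whether patients "find 10 weeks of ACT group therapy an acceptable treatment". Under Data collection and measures, item (7) of the primary outcomes turns this into "the acceptability of the intervention at 12 month follow-up, as assessed by a 5 point likert scale". Three things are rated: helpfulness, satisfaction and likelihood of recommending the treatment. The lowest anchor denotes none of the quality asked about. No other time point is given for this rating, although contacts are planned at 3 and 6 months by telephone.

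The Sample size section plans for attrition: "to allow for loss to follow up, estimated at 30%, we will aim to recruit 58 participants". It adds that "Loss to follow up and intervention and Usual Care Support Group attrition, including reasons, will be recorded to inform power calculations". Reasons for attrition also appear as item (5) of the primary outcomes, next to dropout after randomisation (item 1) and sessions attended (item 4). Interviews come no earlier than the rating: a "semi-structured interview study will be conducted with 12 participants (six ACT; six control) following the 12 month follow-up".

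On safety, the Exclusion criteria describe "a PHQ-9 to screen for suicidal ideation by a clinician at their regular follow-up appointment". The PHQ-9 is not among the instruments listed for follow-up. The document contains no adverse-event wording.

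**The concern.** Acceptability of a short group treatment is best asked soon after it ends, and of everyone allocated to it. The plan asks late, and only of those still in the study at one year. Two problems follow.

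- **Selection.** People who leave early may be the least satisfied, and they never give a rating. A favourable result among those retained could then overstate acceptability in the randomised group.
- **Recall.** Those who do answer are judging something that finished most of a year before. Their weight course and other care in the meantime may colour the answer.

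The result will inform whether and how a definitive trial is run. An analysis plan can describe missing ratings but cannot supply them, so the schedule has to be right in the protocol.

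**Working it through.** **Inputs.** Target 58, expected loss 30% and recommended range 24 to 50 (Sample size); equal allocation (Randomisation); ten weekly sessions (Intervention); rating at 12 months only (primary outcome item 7).

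**1. The protocol's own figure.** Required N = completers / (1 − loss). With 40 completers, 40 / 0.70 = 57.1, rounded up to 58. In reverse, 58 × 0.70 = 40.6. The base of 40 is inferred, since the protocol gives only the range, but 58 fits a 30% loss. The point below does not change this number.

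**2. Ratings lost.** Per arm, 58 / 2 = 29. Expected loss is 0.30 × 29 = 8.7, about 9, leaving about 20 who rate. Over both arms it is 0.30 × 58 = 17.4, about 17. This assumes equal loss in the two arms.

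**3. What can be said about all 29 ACT participants.** Let f be the number of favourable ratings among the 20.

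- Lowest possible share = f / 29
- Highest possible share = (f + 9) / 29
- Width = 9 / 29 = 31.0 percentage points, whatever f is

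Illustration with f = 16 (80% of respondents, assumed): 16 / 29 = 55.2% to 25 / 29 = 86.2%.

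**4. The same bound at 3 months.** The protocol gives no non-response rate for that point, so the rates are assumed.

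| Assumed non-response at 3 months | Missing of 29 | Width |
|---|---|---|
| 10% | 3 | 10.3 points |
| 20% | 6 | 20.7 points |
| 30% | 9 | 31.0 points |

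At 30% the 3-month bound is no narrower, and the gain is in timing alone.

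**5. Delay.** If groups start at baseline (assumed), 52 − 10 = 42 weeks, or 9.7 months, separate the last session from the rating. A later start shortens this, so roughly nine months is a fair description.

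**6. Secondary note: what else would show worsening.**

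| Source | What it gives | What it does not give |
|---|---|---|
| Client Service Receipt Inventory (CSRI) at 3, 6 and 12 months | Primary care, secondary care and A&E use over the previous 3 months | Months 6 to 9; cause or relation to the group |
| HADS and EQ-5D-5L | Change in mood and health status among those followed | Suicidal ideation as such; perceived harm |
| Reasons for attrition | A possible signal from those who leave | Anything from those who stay |

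None of these is stated to record new suicidal ideation or perceived harm from the group.

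**The case against.** The strongest reply is that acceptability does not rest on the rating alone. Items (1), (4) and (5) cover early leavers, and someone who left because the group was unhelpful may well say so when asked why. That stands, and it means the trial is not blind to poor acceptability. However, attendance and dropout also reflect work, travel and health. A reason for leaving is not an answer to the three rated questions.

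A second reply is that the 31-point width arises for any yes/no outcome with this loss. That is also true. It matters here because acceptability is a primary measure and because a contact that could carry the question already exists at 3 months. The 12-month visit is a sensible face-to-face occasion, and the proposal keeps it.

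A third reply is that a response for having been made worse does not fit the satisfaction and recommendation items, where low scores are already unfavourable. That is fair, so it should be a separate item.

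A reader might go further and infer that serious events go unrecorded in this trial. The document does not support that. The CSRI asks about secondary-care and A&E use at each follow-up, and HADS and EQ-5D-5L are repeated. Nor are reasons for attrition kept only for later power calculations: the Sample size section gives that purpose, but item (5) makes them a primary feasibility measure in their own right. A separate safety procedure may also exist outside this document, so the absence of one here does not show that nothing is collected.

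**Conclusion.** The point holds for the timing and reach of the acceptability rating. As written, about 9 of 29 ACT participants would never rate the treatment, and the share of all randomised ACT participants finding it acceptable is bounded only to within about 31 points. This rests on the protocol's 30% loss, equal loss by arm, and the extreme case in which every missing rating could go either way. The roughly nine-month delay rests on groups starting near baseline.

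This is a worthwhile improvement, not a fatal defect: no sample size, alpha or power figure changes, and indirect evidence on early leavers exists. The safety observation is a secondary note only. The protocol shown states no adverse-event procedure and does not repeat PHQ-9 Question 9 after screening, and the partial sources it does have do not cover suicidal ideation or perceived harm.

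**What to change.** Collect the three acceptability items at 3 months as well as at 12, from all randomised participants in both arms, including those who have stopped attending. Because the 3-month contact is by telephone, use a self-completed form, for example by post. Have it returned to a team member who is neither the blinded researcher nor involved in delivering or supervising ACT. If a group is still running at 3 months, send the form after its last session. Add one separate item on whether the group made things worse, and leave the existing items unchanged so that the two time points can be compared. Report the answers descriptively by arm, with the number not responding.

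The cost is one more short form, some non-response to it, and a small risk that an answer reaches the blinded researcher.

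On the secondary note, if a safety procedure exists elsewhere, a sentence citing it is enough. Repeating Question 9 should be considered only with a staffed same-day risk pathway for positive answers, which is a real cost for telephone contacts.
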